## Statistical methods

### Statistical methods for primary and secondary outcomes {20a}

The primary analysis will follow an intention-to-treat approach, comparing the mean differences in changes in systolic blood pressure, fasting plasma glucose levels, and changes in smoking status between individuals assigned to the intervention arm vs control arms. Primary outcomes will be measured at baseline and six months, requiring models that account for repeated measures and the hierarchical structure of participants nested within sites. To compare changes between groups, we will use mixed-effects models for each outcome: linear mixed-effects models for continuous outcomes (SBP, fasting blood glucose) and a mixed-effects logistic regression for the binary outcome (smoking status), each including a random intercept for participants. Fixed effects will include intervention, time (baseline and 6 months), their interaction, and potential confounders. For continuous outcomes, the interaction term represents the difference in mean change between groups. For the binary outcome, it represents the difference in change in log-odds of smoking cessation, with the odds ratio indicating how much greater (or smaller) the change in odds of cessation is for the intervention group relative to control.

Although outcomes may be correlated, the univariate approach is conservative and simplifies interpretation without assuming a multivariate distribution. Sensitivity analyses will use multivariate models accounting for correlations between outcomes. Continuous outcomes will be analyzed jointly using repeated-measures MANOVA or a multivariate linear mixed model with an unstructured covariance matrix. For mixed outcome types, a multivariate logistic mixed model or joint modeling approach will be applied. These models account for both outcome correlations and data hierarchy, allowing estimation of overall intervention effects and assessment of robustness relative to univariate analyses.

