### Participant timeline {13}

The intervention will consist of six months of either the SCALE-NCD intervention or usual care. In the intervention arm, participants will receive FCHVs home visits twice, while receiving SMS messages weekly. Study team visits for follow-up data collection will occur at 3 months and 6 months. A schematic diagram is presented in Figure 3.

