### Sample size {14}

We calculated the required sample size to achieve 90% power for each of the three hypotheses using PASS 2022 software (v22.0.4), with formulations derived from Campbell and Walters (2014)^33^ and Ahn, Heo, and Zhang (2015)^34^. Sample size was calculated for each outcome using a Bonferroni-adjusted method, and the largest required sample size was selected to ensure adequate power for all outcomes. Given the multiple hypotheses corresponding to three different outcomes, we adjusted for multiple comparisons using a Bonferroni correction and set the significance level at 0.05/3 = 0.017 for each test.

For the fasting blood glucose sample size calculation, we assumed a coefficient of variation (COV) of the cluster size of 0.65, a standard deviation of 45.5^27^ and an intra-class correlation coefficient (ICC) of 0.01.^27^ We determined that sample sizes of 90 in the intervention group and 90 in the control group, obtained by sampling 15 clusters with an average of 6 subjects each, were required to detect a difference between the group means of at least −26 mg/dl. After adjusting for a 15% attrition rate, the participant enrollment from each cluster is 9/0.85 = 7, resulting in a sample size of 105 per arm.

For SBP, we assumed the same COV and ICC as 0.01, with a standard deviation of 15.46.^26^ An average of 23 subjects per cluster per arm would achieve 90% power to detect a difference between the group means of at least −5 mmHg. After adjusting for a 15% attrition rate, the participant enrollment from each cluster is 23/0.85 = 27, resulting in a sample size of 405 per arm.

For smoking cessation, we used the test for two proportions in c-RCTs, with formulations from Donner and Klar (2000). We assumed an ICC of 0.01 and a proportion of smoking quitters in the control group of 0.019.^28^ Sample sizes of 450 per arm, obtained by sampling 15 clusters with 30 subjects each, achieve 80% power to detect a difference between the group proportions of 0.05. After accounting for a 15% dropout rate, we require 35 participants in each group, resulting in a total sample size of 525 per group.

Using Bonferroni-adjustment for each outcome and taking the largest sample size is conservative and may overestimate requirements. Despite the outcomes being correlated, this univariate approach ensures adequate power and simplifies interpretation without assuming a multivariate distribution.

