## Data collection and management

### Plans for assessment and collection of outcomes {18a}

In the trial, data will be collected at three time points: baseline (0 months), interim (3 months), and endline (6 months). The types of data collected and its specific timeline has been presented earlier. In addition to data for primary and secondary outcomes, we will collect data for intervention adherence, which will be used for sensitivity analysis. To maintain data quality, several procedures will be undertaken. First, data collection will be entirely digitalized to minimize data entry errors. Trained research staff will enter data directly into the REDCap application on tablets provided by the coordinating center. Each morning, the tablets will be distributed to the research staff, and all devices will be collected back at the end of the day, when staff in coordinating centers will check the condition of tablets and update the operating systems if needed. Data entered by research staff will be monitored daily by the data management team, which is comprised of data managers in the coordinating center and one data manager in Johns Hopkins Bloomberg School of Public Health. Any duplications, missing values, or other data entry errors will be reported to a senior staff member at the coordinating center, who will address the issues by communicating with the field research staff and, when necessary, the investigators. Second, research staff will be trained for data collection techniques through 7-day training prior to the field placement, during which they will be trained on the use of REDCap, verbatim questionnaire administrations, and clinical assessment techniques (e.g. BP measurements, finger prick glucose measurement, height, weight).

Study instruments will be pre-tested with population living outside of the study site to ensure clarity, user-friendliness, and consistency in interpretation among participants.

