### Plans for collection, laboratory evaluation and storage of biological specimens for genetic or molecular analysis in this trial/future use {33}

Laboratory technicians certified in Nepal will collect 5 mL of venous blood sample at the baseline and endline from all participants. HbA1c and lipid panels (total cholesterol, LDL cholesterol, HDL cholesterol, and triglyceride) will be assessed for all participants while fasting plasma glucose will be additionally measured for those who had fasting fingerprick glucose ≥100 mg/dL. All samples will be analyzed following the reference method approved by the International Federation of Clinical Chemistry and Laboratory Medicine (IFCC). All specimens will be properly disposed of after completion of tests. No genetic or molecular analyses are planned for this trial or any ancillary studies.

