### Interim analyses {21b}

Interim analysis for efficacy will be done at 3 months. Given the low-risk nature of this study, there will be no stopping guidelines established.

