### Methods in analysis to handle protocol non-adherence and any statistical methods to handle missing data {20c}

Exploratory sensitivity analysis will be performed by comparing analyses conducted on intention-to-treat population vs per-protocol (i.e. adherent) population. For any variable in the final dataset that has more than 5% missing values, a series of sensitivity analyses will be performed, such as comparing analyses conducted on complete cases vs those conducted using an appropriate imputation framework.

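### The primary SBP model is limited to baseline and 6 months although a 3-month efficacy analysis implies month-3 outcome data; if SBP is among them, leaving it out exposes the 6-month effect to avoidable dropout bias

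*Protocol article*

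**What the plan says.** Three sections describe a 3-month assessment.

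- Participant timeline {13}: "Study team visits for follow-up data collection will occur at 3 months and 6 months", with no restriction to one arm.
- Plans for assessment and collection of outcomes {18a}: "data will be collected at three time points: baseline (0 months), interim (3 months), and endline (6 months".
- Interim analyses {21b}: "Interim analysis for efficacy will be done at 3 months".

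Statistical methods {20a} describes two visits only: "Primary outcomes will be measured at baseline and six months, requiring models that account for repeated measures". The model follows suit: "Fixed effects will include intervention, time (baseline and 6 months), their interaction, and potential confounders". This applies to all three primary outcomes.

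Two further sections bear on the point. Section {33} says that technicians "will collect 5 mL of venous blood sample at the baseline and endline from all participants", so fasting plasma glucose has no month-3 value. Section {20c} handles missing data through sensitivity analyses once a variable has more than 5% missing, "comparing analyses conducted on complete cases vs those conducted using an appropriate imputation framework". It names no imputation model and does not mention month-3 values.

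**The concern.** An efficacy analysis at 3 months needs an efficacy outcome at 3 months in both arms. The statement that primary outcomes are measured at baseline and six months therefore sits badly with the interim plan, unless the interim look uses secondary outcomes only. Glucose is ruled out by the blood-sampling schedule. SBP and smoking status need no laboratory and are the likely candidates.

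If SBP is recorded at month 3, the two-level time factor discards it. A likelihood-based mixed model is valid when dropout depends only on data in the model. With two visits, that covers dropout related to baseline SBP but not dropout related to SBP at month 3. Participants know their allocation, so dropout that tracks early response differently by arm is conceivable. What is at stake is the 6-month SBP effect, one of the three primary results.

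**Working it through.** **Inputs from the protocol (Sample size {14}).** SBP standard deviation 15.46 mmHg; target difference 5 mmHg; ICC 0.01; coefficient of variation of cluster size 0.65; 15 clusters per arm; 23 analysable participants per cluster; 90% power; 15% attrition with no timing given. For alpha, the plan "set the significance level at 0.05/3 = 0.017 for each test"; two-sided testing is assumed because sidedness is not stated.

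**Step 1: reproduce the plan's SBP figure.**

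- Design effect = 1 + ((1 + CV²)m − 1) × ICC = 1 + (1.4225 × 23 − 1) × 0.01 = 1.317.
- Effective n per arm = 15 × 23 / 1.317 = 345 / 1.317 = 261.9.
- Standard error = 15.46 × √(2 / 261.9) = 1.35 mmHg.
- Power = Φ(5 / 1.351 − 2.394) = Φ(1.307) = 0.904.

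The smallest cluster size reaching 90% is 23, so the figure reproduces. The standard error of 1.35 mmHg is a yardstick for the biases below.

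**Step 2: simulate dropout after month 3.** SBP was generated at 0, 3 and 6 months for 400,000 participants per arm, with SD 15.46 at each visit and a true month-6 effect of −5 mmHg. Loss after month 3 was set at 15% per arm, with logistic dependence on month-3 SBP.

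These assumptions are not in the protocol:

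- a month-3 effect of −3 mmHg;
- correlation between adjacent visits, and between baseline and month 6, of 0.6 and 0.5, or of 0.7 and 0.6;
- dropout slopes from 0 to 1 (in absolute value) per SD of month-3 SBP.

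Two estimates of the arm difference in change were compared. The two-visit estimate predicts missing month-6 values from baseline only. The three-visit estimate predicts them from baseline and month 3 without constraining the correlations, as an unstructured covariance would.

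**Results.** Each cell gives the value for correlations 0.6/0.5, then for 0.7/0.6.

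| Dropout slope on month-3 SBP (intervention / control) | Full data | Two visits | Three visits | Error, two visits |
|---|---|---|---|---|
| 0 / 0 | −5.01; −4.98 | −4.99; −4.99 | −5.00; −4.99 | 0.02; −0.01 |
| 0.5 / 0.5 | −5.00; −4.98 | −5.01; −4.97 | −5.01; −4.97 | −0.01; 0.01 |
| 1 / 1 | −5.04; −4.95 | −5.05; −4.94 | −5.06; −4.95 | −0.01; 0.01 |
| 0.5 / 0 | −5.00; −4.91 | −5.34; −5.23 | −5.00; −4.91 | −0.34; −0.32 |
| 1 / 0 | −4.97; −5.05 | −5.61; −5.66 | −4.98; −5.05 | −0.64; −0.61 |
| −0.5 / 0.5 | −4.98; −4.99 | −4.30; −4.37 | −4.98; −5.01 | 0.68; 0.62 |
| 1 / −1 | −5.02; −4.97 | −6.31; −6.16 | −5.03; −4.95 | −1.29; −1.19 |

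The error can go either way: an overstated benefit in rows 4, 5 and 7, an understated one in row 6. The largest, 1.29 / 5, is 26% of the target difference and close to one standard error (1.29 / 1.35 = 0.96). The three-visit estimate stays within 0.02 mmHg of the full-data value throughout.

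**Step 3: timing of loss.** The 15% is total attrition. If only half of it (7.5%) falls after month 3, the error roughly halves. For intervention-arm dependence at slope 0.5 it is 0.15 to 0.21 mmHg, or 3 to 4% of 5 mmHg. Participants lost before month 3 gain nothing from the extra visit.

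**Step 4: precision.** When dropout is random, adding month 3 lowers the variance by only about 2 to 3%. The case for it rests on robustness to dropout.

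**The case against.** The strongest objection is that the text shown never says SBP is measured at month 3. Section {18a} refers back to a schedule, and the timeline figure is not reproduced in the copy reviewed. The only month-3 content named in the text is the number of home visits that intervention participants report (section {11c}). The interim section names no outcome. This stands: month-3 SBP is an inference, so the fix must be conditional on it.

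Second, comparing baseline with 6 months is a standard, valid analysis of a 6-month endpoint, and the bias needs dropout that tracks month-3 SBP differently by arm. The protocol gives no evidence that this will happen, and the text does not say that participants are told their month-3 readings. The scheduled volunteer measurements fall at 0 to 1 and 4 to 5 months. Dropout prompted by the later visit would be only partly explained by month-3 SBP, so the near-complete repair above belongs to the simulated mechanism. This also stands, and it limits the size of the point.

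Third, the imputation sensitivity analysis could use month-3 values, and 15% attrition would trigger it. That helps only in part: it is not specified to do so, and it leaves the primary estimate unchanged. Nor can the whole matter be left to an analysis plan, because the protocol itself fixes the two-level time factor.

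A reader might infer that the two-visit model will bias the SBP result, or that SBP readings certainly exist and are being thrown away. The documents support neither.

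**Conclusion.** The sections disagree on when primary outcomes are measured, and that needs correcting whatever the answer. The consequence for SBP is conditional on two things: SBP is recorded at month 3, and dropout after month 3 depends on it differently in the two arms. Under both conditions and the assumed correlations and slopes, the two-visit estimate is off by about 0.3 to 0.6 mmHg (one arm) or 0.6 to 1.3 mmHg (opposite directions) if all 15% is lost after month 3, and by about half that if half is. With no dependence, or equal dependence in both arms, there is no bias.

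The point could extend to smoking status, for which no size was computed. It does not extend to fasting plasma glucose.

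**What to change.** 1. State in section {20a} which primary outcomes are recorded at month 3, and make this agree with {13}, {18a} and {21b}. Name the outcome or outcomes used in the 3-month efficacy analysis.
2. If SBP is recorded at month 3, fit the SBP model with time as a three-level factor (0, 3 and 6 months), arm-by-time terms and an unstructured within-participant covariance. The participant random intercept now planned is not enough by itself, because it forces equal correlation between all pairs of visits.
3. Keep the arm difference in change from baseline to 6 months as the single primary SBP estimate. Leave fasting plasma glucose at two visits.

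The cost is a sentence or two in the analysis section, one more time level and its covariance parameters. If SBP is already recorded at month 3, no new data are needed. The estimand, the alpha and the sample size do not change. If SBP is not recorded then, only item 1 applies. The change is best made before the 3-month efficacy analysis.

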## Assignment of interventions: allocation

### Sequence generation {16a}

Randomization will be conducted at the cluster level, treating wards in Pokhara Metropolitan city as a unit of analysis. Since there are odd number of wards in Pokhara Metropolitan City, three small wards (wards 1, 2, and 3) and two small wards (wards 4 and 5) will be combined respectively, forming a total of 30 clusters (independent 28 wards and 2 combined wards). These total of 30 clusters will be randomly assigned to either the intervention or the control arm in a 1:1 ratio. Randomization of clusters will be performed using stratified permuted block randomization, stratified by population size of wards. Wards with less than 10,000 people, between 10,000 and 30,000 people, and greater than 30,000 people are categorized to small, medium, and large, respectively. Three sequences were created by choosing blocks of size 2 (AB) and 4 (AABB) with equal probability. The resulting blocks were permuted at random and then concatenated.

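### The primary models name a participant random intercept but no ward term, contradicting the protocol's own nesting requirement, so type I error can exceed the 0.0167 level

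*Protocol article*

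**What the plan says.** All references are to the protocol article.

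- **Sequence generation {16a}:** "Randomization will be conducted at the cluster level, treating wards in Pokhara Metropolitan city as a unit of analysis". Five small wards are merged into two clusters, giving 30 in all, and "These total of 30 clusters will be randomly assigned to either the intervention or the control arm in a 1:1 ratio".
- **Sample size {14}:** the calculations allow for clustering, with "an intra-class correlation coefficient (ICC) of 0.01" for glucose and the same value for SBP and smoking. A cluster-size coefficient of variation (COV) of 0.65 is stated for glucose and carried over to SBP. For multiplicity, the plan "set the significance level at 0.05/3 = 0.017 for each test".
- **Statistical methods {20a}:** the design is described as "requiring models that account for repeated measures and the hierarchical structure of participants nested within sites". The next sentence specifies a linear mixed model for SBP and glucose and a mixed logistic model for smoking, "each including a random intercept for participants". The fixed part is then listed: "Fixed effects will include intervention, time (baseline and 6 months), their interaction, and potential confounders". For the continuous outcomes, "the interaction term represents the difference in mean change between groups".

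The multivariate sensitivity models in the same section are said to handle the data hierarchy, but no ward term is named for them either.

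**The concern.** The methods section sets a requirement and then specifies a model that does not meet it. A participant intercept handles the repeated measures on one person. It does nothing for the correlation between different people in the same ward, and the ward is what was randomised. An analyst who fits the model as stated treats participants in a ward as independent, although the sample size was enlarged because they are not.

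At stake is the standard error of the treatment contrast in the primary analysis. If it is too small, intervals are too narrow, p-values too low, and the Bonferroni level is not held. The error runs towards false positives.

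**Working it through.** **Inputs (Sample size {14}; Sequence generation {16a}).** 15 clusters per arm; ICC 0.01; COV 0.65 for SBP and glucose. SBP: 23 per cluster, SD 15.46, difference 5. Glucose: 6 per cluster, SD 45.5, difference 26. Smoking: 30 per cluster, 0.019 against 0.069. Sidedness is not stated; two-sided α = 0.05/3 is assumed, so z = 2.394.

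**Step 1. Design effects.** DE = 1 + ((1 + COV²)m − 1) × ICC.
- SBP: 1 + (1.4225 × 23 − 1) × 0.01 = 1.317
- Glucose: 1 + (1.4225 × 6 − 1) × 0.01 = 1.075
- Smoking, equal cluster sizes: 1 + (30 − 1) × 0.01 = 1.29

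**Step 2. Reproduce the plan's power.** For the two means, power = Φ(difference/SE − 2.394), with SE = SD × √(2 × DE/n).
- SBP, n = 345: SE = 15.46 × √(2 × 1.317/345) = 1.351; 5/1.351 = 3.70; power 0.904 (plan: 90%)
- Glucose, n = 90: SE = 45.5 × √(2 × 1.075/90) = 7.03; 26/7.03 = 3.70; power 0.904 (plan: 90%)
- Smoking, n = 450: SE = √(1.29 × (0.019 × 0.981 + 0.069 × 0.931)/450) = 0.0154; power 0.802, or 0.797 with a pooled variance (plan: 80%)

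The plan's figures reproduce only with the clustering allowance included, so the sizing assumes an analysis that accounts for wards.

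**Step 3. Error if the analysis omits the ward and ICC 0.01 applies to the tested contrast.** True α = 2 × (1 − Φ(2.394/√DE)).

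| Outcome | DE | True α | Ratio to 0.0167 | SE understated by (1 − 1/√DE) |
|---|---|---|---|---|
| SBP | 1.317 | 0.037 | 2.2 | 13% |
| Glucose | 1.075 | 0.021 | 1.26 | 4% |
| Smoking | 1.29 | 0.035 | 2.1 | 12% |

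**Step 4. SBP and glucose are tested on change.** With both measurements complete, the arm-by-time test in a participant-intercept model equals a two-sample t-test on change. Let the ICC at one time point be 0.01, the within-person correlation 0.5 (assumed), and r the correlation of a ward's effect between baseline and 6 months. In units of the single-time variance:
- variance of change = 2 × (1 − 0.5) = 1
- ward part of change = 2 × 0.01 × (1 − r)
- ICC of change = 0.02 × (1 − r)

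| r | ICC of change | SBP DE | SBP true α | SBP α, simulated |
|---|---|---|---|---|
| 1 (ward effect constant) | 0 | 1.000 | 0.0167 | 0.017 |
| 0.8 | 0.004 | 1.127 | 0.024 | 0.024 |
| 0.5 | 0.010 | 1.317 | 0.037 | 0.035 |
| 0 | 0.020 | 1.634 | 0.061 | 0.061 |

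The simulation used 20,000 trials per case. For glucose at r = 0, DE = 1 + (1.4225 × 6 − 1) × 0.02 = 1.151 and α is about 0.026; the simulated range over the same values of r was 0.016 to 0.025. The protocol gives neither r nor any ICC for change.

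**Step 5. Smoking.** Under Eligibility criteria {10}, a current smoker smokes daily, so those who enter as smokers all have the same status at baseline. The contrast is in effect the 6-month outcome, and there is no baseline ward effect to subtract. The ward ICC therefore stays in the comparison.

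**The case against.** **The list of random effects may be incomplete.** The models are said to include a participant intercept, which need not mean they contain nothing else. The preceding sentence asks for nesting, and the ward is called the unit of analysis. An analysis plan that is not shown may add the ward. This stands in part: the documents do not show that the trial will ignore clustering. But the article states both the random and the fixed part of the primary model, and the randomised level is in neither. That is a contradiction in stated text, not detail deferred.

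**A reader might infer that the plan doubles its type I error.** The figures in Step 3 invite this, and their sum (0.037 + 0.021 + 0.035 = 0.093 against 0.05) even more so. The documents do not support it as a fact of the plan. It requires ICC 0.01 to hold for change, which the sample size section does not say. For SBP the result can be no inflation at all, and glucose is only modestly affected under any value tried. The sum is also only an upper bound on the family-wise error.

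**The smoking figure is not the error of the stated model.** This stands. It comes from comparing two proportions, not from a logistic model with a participant intercept and an arm-by-time term, which is poorly identified when baseline status does not vary. Using COV 0.65 would raise it to 0.044, but the protocol states no COV for smoking.

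**A reader might infer that no positive result could be trusted.** That goes too far. Standard errors understated by about 13% (SBP) or 4% (glucose) change borderline results, not clear ones.

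**Conclusion.** The contradiction is certain: Statistical methods {20a} requires the nesting to be modelled, then specifies primary models without the randomised level, at odds with the ward randomisation and the ICC-based sample size. The size of the consequence is not certain.

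- **SBP:** per-test error between about 0.017 and 0.06 against 0.0167; 0.037 if ICC 0.01 holds for change.
- **Glucose:** between about 0.017 and 0.025; 0.021 if ICC 0.01 holds for change. This is minor.
- **Smoking:** about 0.035 by approximation with equal cluster sizes; the ward ICC does not cancel.

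These rest on two-sided tests, 15 clusters per arm and, for the ranges, a single-time ICC of 0.01, within-person correlation of 0.5 and complete pairs of measurements. The no-inflation end needs wards not to differ at all in their change over time. That cannot be presumed when each ward's own volunteers deliver the intervention. The point should be corrected because it touches all three primary analyses and the correction is cheap.

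**What to change.** State in Statistical methods {20a} how ward-level correlation enters each tested contrast, using the 30 randomised clusters as the ward level.

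- **SBP and glucose:** a ward random intercept plus a ward-by-time random effect, with participants nested in ward. Alternatively, model the 6-month value adjusted for baseline with a ward random intercept. Adding a ward intercept alone to the present interaction model is not enough, because a constant ward effect cancels from change and the ward-by-time variance would still be left out.
- **Smoking:** a ward random effect, or generalised estimating equations clustered on ward, for the 6-month outcome among baseline smokers.
- **Throughout:** a small-sample correction for 30 clusters, for example Satterthwaite or Kenward-Roger degrees of freedom in the linear models and a bias-corrected variance in the estimating equations. An equivalent cluster-level analysis would also do. The choice among these can be left to the analysis plan; that the ward enters the contrast should not be.

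Cost: about one sentence of text and somewhat wider, correct confidence intervals. No new data or participants.

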### Implementation {16c}

Using the allocation sequence developed by an independent biostatistician, 30 clusters will be assigned to either the intervention or the control arm. When research staff recruit a participant from an intervention cluster, the coordinating centre in Nepal will notify a trained FCHV working in the respective cluster, who will visit the home of the participant within a month from the enrollment. The coordinating centre will also subsequently notify a SMS message company in Nepal, so that text messages will be scheduled and sent to the participant between 9–10 am on weekly basis. Research staff will recruit a participant in control clusters with the same approach, where the coordinating centre will notify neither FCHVs nor the SMS company.

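### As stated, baseline confounders do not adjust the SBP and glucose effects: main effects cancel from the arm-by-time interaction, so imbalance that predicts change stays in the estimate

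*Protocol article*

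**What the plan says.** All of the model description is in the protocol article, section {20a}, Statistical methods for primary and secondary outcomes.

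- Analysis set and visits: "The primary analysis will follow an intention-to-treat approach", and "Primary outcomes will be measured at baseline and six months".
- Model for SBP and glucose: linear mixed models, "each including a random intercept for participants".
- Fixed effects: "Fixed effects will include intervention, time (baseline and 6 months), their interaction, and potential confounders".
- Effect of interest: "For continuous outcomes, the interaction term represents the difference in mean change between groups".

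Intervention by time is the only interaction named. The section does not name the confounders or say whether any of them vary over time. It mentions no confounder-by-time term, no baseline value used as a covariate and no constrained baseline.

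Two other sections bear on imbalance. Implementation {16c} describes enrolment from wards whose arm is already set ("When research staff recruit a participant from an intervention cluster"). Recruitment {15} draws people at random from the voter list within voting centre, sex and four age bands.

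**The concern.** A reader will take the reported SBP and glucose effects as adjusted for confounding. If the confounders are baseline characteristics entered as main effects, they adjust the arm difference in level but leave the difference in change untouched. The effect would be labelled adjusted while being, in substance, the raw difference in mean change.

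This affects two of the three primary outcomes. There are only 15 wards per arm, and people consent in wards that already have an arm, so some imbalance in factors that predict change is plausible. Naming the covariates later would not cure this, because any further baseline factor added as a main effect would be equally inert. The exact result applies to the linear models only and does not carry over to the logistic model for smoking.

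**Working it through.** **1. The plan's own SBP figure, which supplies the scale.** Inputs from Sample size {14}: SD 15.46, difference 5 mmHg, ICC 0.01, coefficient of variation of cluster size 0.65, 15 clusters of 23 per arm, 90% power, and "set the significance level at 0.05/3 = 0.017 for each test" (taken as two-sided).
- Individually randomised n per arm: 259.
- Design effect: 1 + ((0.65² + 1) × 23 − 1) × 0.01 = 1.317.
- 259 × 1.317 = 341, against 15 × 23 = 345 stated. Power at 345 is 90.4%, so the figure reproduces.
- Planning standard error: √(2 × 15.46² / 345 × 1.317) = 1.35 mmHg.

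**2. The algebra.** For participant i at visit t (0 or 1), with a baseline covariate X:

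Y(i,t) = a + b·arm + c·t + d·arm·t + g·X + u(i) + e(i,t)

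The change is Y(i,1) − Y(i,0) = c + d·arm + e(i,1) − e(i,0). X has gone. The within-person sum carries X but gives no separate information on d, because b is free. With complete pairs, the estimate of d is the raw difference in mean change whether or not X is in the model.

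**3. Numerical check at the trial's size** (30 clusters of 23, SD 15.46, true effect −5, two imbalanced covariates of which one predicts change, assumed within-person correlation parameter 0.5, 10 runs).

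| Comparison of arm-by-time estimates | Difference (mmHg) |
|---|---|
| With v. without main effects, complete pairs | at most 9 × 10⁻¹³; standard errors equal |
| Same, cluster and participant intercepts (one data set) | none: −5.9696 both ways |
| With v. without main effects, 15% covariate-dependent dropout | mean 0.04, maximum 0.09; SE about 1.28 |
| Covariate-by-time v. main effect only | about 0.85 |

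The simulation also contained a constant +3 mmHg arm difference at both visits. It cancels from the interaction.

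**4. Imbalance in a factor that predicts change.** Bias = imbalance × extra fall. Type I error = P(|Z + bias/1.351| > 2.394). The protocol gives neither the imbalance nor the extra fall; both are assumed.

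| Imbalance | Extra fall (mmHg) | Bias (mmHg) | Type I error |
|---|---|---|---|
| 5 points | 2 | 0.10 | 1.70% |
| 5 points | 5 | 0.25 | 1.85% |
| 15 points | 2 | 0.30 | 1.94% |
| 15 points | 5 | 0.75 | 3.5% |

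Nominal is 0.05/3 = 1.67%. A bias of 0.75 is 15% of the 5 mmHg target.

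**5. Chance imbalance in the baseline outcome.** If the arms differ by d at baseline through chance, regression to the mean shifts the change estimate by −(1 − ρ)d, where ρ is the correlation between baseline and 6 months. The protocol does not state ρ; 0.3, 0.5 and 0.7 are assumed.
- SBP, d of one standard error (1.35 mmHg): shifts of −0.95, −0.68 and −0.41 mmHg.
- Glucose: the standard error is √(2 × 45.5² / 90 × 1.075) = 7.03 mg/dL, where 1.075 = 1 + ((0.65² + 1) × 6 − 1) × 0.01. One such imbalance gives shifts of −4.9, −3.5 and −2.1 mg/dL, against a target of 26.
- Over repeated trials this averages to zero, so its cost is precision. The variance of a change analysis relative to baseline-adjusted analysis is 2(1 − ρ)/(1 − ρ²) = 1.54, 1.33 and 1.18.

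**The case against.** **The text does not say main effects or time-fixed.** This is true. A covariate measured at each visit, such as current medication, would not cancel. Covariate lists and functional form are also commonly left to a statistical analysis plan, which is not at hand. What remains is that the article gives the model structure, names a single interaction and calls the covariates confounders. Baseline main effects are the natural reading, and a covariate list added to that structure would not repair it.

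**A reader might infer that any baseline imbalance contaminates the effect.** It does not. The algebra that makes the covariates inert also removes a difference that is equal at both visits. Likewise, it is too strong to say that adjustment can never move the estimate: with dropout it moves it slightly.

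**A reader might infer that this adjustment is the plan's declared safeguard against recruiting after allocation.** Neither section {20a} nor {16c} gives it that purpose. Random selection within sex and age strata also limits whom staff approach, though it does not rule out differential consent.

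**The largest figure is extreme.** This stands. An extra fall of 5 mmHg equals the whole target effect. For a factor with 50% prevalence, a 15-point gap is 0.15 / √(2 × 0.25 / 345 × 1.317) = 3.4 standard errors, which would need strongly selective enrolment. The milder scenarios raise the type I error only to between 1.7% and 1.9%.

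**Conclusion.** The point holds in limited form. For SBP and glucose, time-fixed confounders entered only as main effects do not adjust the arm-by-time estimate. This is exact for participants with both visits and true to within about 0.09 mmHg in the runs with 15% attrition. What stays in the estimate is imbalance in covariates that predict change, and chance imbalance in the baseline outcome through regression to the mean.

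The cancellation is algebra and rests only on the natural reading of the fixed-effects sentence. The consequences rest on assumed imbalances, slopes and correlations: a bias of 0.10 to 0.75 mmHg and a type I error of about 1.7% to 3.5%, with the upper end needing both assumptions to be extreme. A headline of doubled type I error is therefore not supported as an expectation. No sample-size figure changes. This is a cheap improvement to the model statement; it does not invalidate the trial.

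**What to change.** In section {20a}, for SBP and glucose, replace the fixed-effects sentence with one of these:

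1. Model the 6-month value with the baseline value of the same outcome and prespecified baseline covariates as predictors. The baseline outcome must be included; without it the model brings back the baseline-level differences that a change analysis removes.
2. Use a mixed model with the arm means constrained equal at baseline, plus covariate-by-time terms.
3. Keep the stated model and add covariate-by-time terms. This deals with covariates that predict change, but not by itself with regression to the mean in the baseline outcome.

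In each case include a ward (cluster) effect, fix the covariates before unblinding, and report the unadjusted estimate alongside. The unadjusted estimate matters because options 1 and 2 treat a baseline difference in the outcome as chance, whereas selective enrolment could produce a lasting one.

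The cost is a sentence or two and a few degrees of freedom. No extra data or participants are needed.
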